## Abstract

**Background:**

Aggressive conduct among delinquents presents a pervasive issue, bearing substantial implications for not only society at large but also for the victims and the individuals displaying the aggression. Traditional approaches to treating aggression regulation deficiencies generally employ Cognitive Behavioral Therapy (CBT) in conjunction with analog role-playing exercises. A body of research supports the efficacy of various therapeutic models for aggression regulation, including Responsive Aggression Regulation Therapy (Re-ART). Role-playing within a therapeutic context has been shown to contribute significantly to reductions in violent reoffending. However, the practical application of these skills in real-world settings remains challenging due to the inherent risk of aggressive outbreaks. Additionally, the conventional role-playing scenarios, often conducted in a therapy room, lack contextual realism and may induce role confusion between the patient and the therapist. Virtual Reality (VR) technology could offer a viable solution to these limitations by allowing for skill training in both behavioral and cognitive domains within a realistic yet safe and controlled setting. The technology also facilitates real-time awareness of emotional states and tension levels in the patient. This paper describes the study protocol of a randomized controlled trial in which Re-ART offered in a virtual environment (Re-ART VR) is compared to Re-ART offered as treatment as usual.

**Methods and analysis:**

Adult forensic outpatients with aggression regulation problems are randomly assigned to either Re-ART VR or Re-ART. The *Controlling Skills*, *Influence of Thinking* and *Handling Conflicts* modules will be offered to both groups during 3–6 months. Pre- and post-intervention measurements are performed. The primary outcome measurement is the degree of aggression regulation, while secondary outcome measurements include impulsivity and cognitive biases. Additionally, patient motivation and therapist motivation are expected to act as moderating factors.

**Discussion:**

To date, scarcely previous research has been done on the effectiveness of VR in treatment of aggression regulation problems in forensic outpatients. Forensic outpatients who do not benefit sufficiently from mainly CBT-based interventions may benefit more from experiential learning. The unique capabilities of VR in this regard have the potential to enhance the treatment effect.

**Clinical trial registration**: [https://clinicaltrials.gov/], identifier [NL78265.018.21].

## Introduction

1

Aggressive behavior poses a significant challenge to society, impacting not only the individuals involved but also the wider community. Despite a decline in international crime rates among young adult offenders (Berghuis and De Waard, 2017; Fernández-Molina and Bartolomé Gutiérrez, 2020), the persistence of violent behaviors like threats, abuse, vandalism, and public order disturbances remains a major concern due to their profound consequences on both victims and society (e.g., Aarten et al., 2020). Violent behavior has significant financial implications, affecting various aspects such as victims’ costs and criminal justice expenditures (Cohen and Piquero, 2015), and legal financial obligations for offenders (Pleggenkuhle, 2018). Moreover, violent offenders often exhibit high rates of recidivism, perpetuating the cycle of harm (Falk et al., 2014; Alper et al., 2018; Weijters et al., 2018; Stewart et al., 2019). Improving therapy for violent offenders is essential. Research indicates that integrating elements of Cognitive Behavioral Therapy (CBT) with Virtual Reality (VR) holds promise. For this reason, this study focuses on the impact of VR in treatment of aggression regulation problems.

The primary approach to treating aggression regulation problems involves CBT. Overall, research highlights the significant impact of interventions incorporating role-playing, cognitive skills, and homework assignments in treatment, leading to notable decreases in general and/or violent re-offending compared to interventions lacking these elements (Jolliffe and Farrington, 2007; Papalia et al., 2019; Hoogsteder et al., 2023a). Responsive Aggression Regulation Therapy (Re-ART) is an example of an aggression regulation intervention that combines CBT-elements with role-playing and experiential exercises such as chair techniques, imaginations, and mindfulness exercises (Hoogsteder and Bogaerts, 2018). Initially, Re-ART was developed for boys and girls aged 16–21 years in residential care with severe aggression regulation problems and a moderate to (very) high recidivism risk. Its effectiveness is now demonstrated in young adults in both in- and outpatient forensic treatment (Hoogsteder et al., 2014a,b; Schippers et al., 2020). More specifically, compared to control groups receiving treatment as usual, Re-ART showed to improve coping skills, treatment motivation, and diminishes impulsivity and cognitive distortions, leading to a significant reduction in both violent and general recidivism after 2 and 3 years (Hoogsteder et al., 2018, 2021). By integrating evidence-based elements, Re-ART aims to provide a promising approach to address and manage aggressive delinquent behavior. However, despite these positive outcomes, the effect of aggression regulation therapy remains moderate, indicating the need for further refinements in treatment strategies (Papalia et al., 2020; McIntosh et al., 2021).

A new technology that seems promising in increasing the treatment effects of role playing, among other things, is VR. Role-playing in VR presents distinct advantages, allowing controlled exposure to stimuli that might be too risky or harmful in real-life situations, thereby safeguarding others. Moreover, the use of avatars in VR role play eliminates role confusion that can occur especially when therapists engage in so-called analog role-play with their patients (Fromberger et al., 2014). VR is valued for its ability to facilitate implicit and experiential learning (Slater and Sanchez-Vives, 2016; Kip et al., 2018). Comparative studies, such as that by Park et al. (2011), indicate that VR role-playing outperforms analog role-playing in enhancing conversational skills, assertiveness, treatment interest and skill generalization. Additionally, VR requires active engagement from therapists and patients. This is expected to boost patient motivation and healthcare professional enthusiasm, potentially enhancing therapeutic relationships and treatment effectiveness (Kip et al., 2019a,b).

Previous research investigating the application of VR in treating mental disorders has demonstrated its effectiveness for specific phobias, as well as other clinical conditions such as obsessive-compulsive disorder, eating disorders, autism, schizophrenia, and post-traumatic stress disorder (Eichenberg and Wolters, 2012; Turner and Casey, 2014; Valmaggia et al., 2016; Freeman et al., 2017; Wiebe et al., 2022). While it is generally acknowledged that VR shows promise as a valuable addition to existing treatments, further research is required to fully understand its effectiveness. In the context of forensic treatment, the use of VR in forensic mental health care is expected to have added value (Kip et al., 2019a,b; Roggeman et al., 2021), but research is still in its early stages. Evidence suggests the effectiveness of applying VR in forensic setting (Jo et al., 2022; Johnston et al., 2023). Findings from an initial randomized controlled trial indicated that an intervention that integrated VR with serious gaming did not yield superior results in reducing anger and aggressive behavior compared to the control condition among forensic psychiatric outpatients with aggression regulation issues. Nevertheless, qualitative data revealed that participants reported gaining more insight into their own behavior and the behavior of others (Smeijers et al., 2021). As far as our knowledge extends, no other studies have yet been conducted on the effectiveness of VR in treating aggression regulation problems within an outpatient forensic setting. Thus, more research is needed to explore its potential benefits in this specific domain (Sygel and Wallinius, 2021).

In forensic inpatient studies involving VR, positive pre-post effects were observed on self-reported direct aggression and hostility, anger control and impulsiveness compared to a waiting list control group. However, these effects ceased to exist after a 3-month follow-up period (Klein Tuente et al., 2020). The authors put forth several explanations for these findings, with the closed setting being the most significant factor. The confined environment made it challenging to apply the skills learned in the VR setting to real-life situations effectively. Moreover, the patients were not actively encouraged to practice their newly acquired skills between sessions or given homework assignments. Furthermore, the research protocol lacked options for personalized interventions, as advocated in the Risk-Need-responsivity model (RNR), the most applied rehabilitation model in forensic treatments (Andrews and Bonta, 2017). These limitations likely contributed to the diminished medium-term impact of the VR intervention. To the best of our knowledge, no studies have been conducted to compare inpatient and outpatient groups regarding the transfer of acquired skills into practical application. However, one could hypothesize that the effectiveness of VR within an outpatient setting may be higher due to the increased opportunity for patients to practice and apply the learned skills in their daily lives. This is especially true considering that homework assignments are a standard component of the Re-ART treatment.

The primary objective of this Randomized Controlled Trial (RCT) is to assess the potential benefits of incorporating VR into the existing Re-ART. More specifically, the study aims to examine the extent to which VR enhances the degree of aggression regulation among aggressive forensic outpatients (Re-ART VR) above and beyond the effects found in their counterparts receiving the regular Re-ART intervention. The effect of cognitive biases and impulsivity as determinants of aggressive behavior is examined as secondary outcome measures as well. Moreover, the study will explore motivation as a moderating variable, both among patients undergoing treatment and among the therapists delivering the intervention. The hypothesis posits that patients treated with Re-ART VR will experience greater enhancements in the degree of aggression regulation, a more substantial reduction in cognitive biases and impulsivity compared to those receiving regular Re-ART. Additionally, it is expected that higher levels of patient motivation and therapist motivation will contribute to more pronounced improvements.

## Methods and analysis

2

### Study design

2.1

An RCT with a pretest-posttest design will be carried out in which forensic outpatient with aggression regulation problems are being assigned to either Re-ART using VR (Re-ART VR) or regular Re-ART. Pre- (prior to the Controlling Skills module—T1) and post-intervention (at the end of the Handling Conflicts module—T2) measurements are performed. Figure 1 presents the flow diagram.

**Figure 1 fig1:**
[figure not shown]
Flow diagram.

### Setting

2.2

The study will be conducted at a large Dutch center for forensic outpatient treatment. Mainly CBT-based interventions are offered to juvenile and adult offenders who, due to their offense behavior, (are prone to) encounter police force or judicial authorities. Offense behaviors can vary from aggression in or outside the family, property offenses with or without violence, or sexual offenses. Several general exclusion criteria for treatment - clinically assessed at the registration and intake phase - are applicable. General exclusion criteria for treatment are acute psychosis and serious addiction problems that require supervised detoxification, due to the absence of the specific prerequisites at the treatment center for addressing these issues. Patients enter treatment on a voluntary or mandatory basis. In both scenarios, the patients participating in the study meet the eligibility criteria for Re-ART. Voluntary treatment indicates that the patient enters treatment on his own initiative, on referral of a general practitioner or another mental health care institute. Mandatory treatment means that treatment is imposed by a judge. In these cases, a probation officer fulfills the supervisory role.

### Participants

2.3

The study includes adult (18 years or older) male patients who meet the inclusion criteria for Re-ART, which entails exhibiting aggressive behavior and having a moderate to high risk of recidivism. The study takes place at four out of the thirteen locations of the treatment center, as these four locations are equipped with VR sets. Therapists receive training in CleVR’s VR-CBT software (see section 2.6.4.1), either from a CleVR trainer or from colleagues with VR experience, gaining extensive experience through their regular clinical practice. The main researcher provides instructional materials, including videos demonstrating VR exercises.

#### Sample size

2.3.1

To ensure sufficient statistical power for detecting significant effects in our repeated measures ANCOVA with within-between interaction, an *a priori* power analysis was conducted (G*Power; Faul et al., 2009). Using an expected effect size (f) of 0.25, a significance level (α) of 0.05, and a desired power (1-β) of 0.80, the calculation revealed that a total sample size of 34 participants is required for the study (17 in each condition). The analysis assumes two groups (Re-ART VR vs. regular Re-ART) with two measurement points (pre- and post-intervention), a correlation of 0.5 among repeated measures, and no sphericity correction (ε = 1).

#### Recruitment

2.3.2

Therapists will approach patients who meet the study inclusion criteria (see Figure 1). Patients who meet the Re-ART inclusion criteria (e.g., moderate to high recidivism risk, poor impulse control) are considered for study inclusion, except for those who receive concurrent interventions (e.g., trauma-focused therapy or treatment of substance abuse) during the study. This is done to prevent potential interference with the efficacy measurements in the current study. Following a comprehensive oral and written explanation of the study, patients who meet the study inclusion criteria (adult, male) will be requested to provide informed consent during discussion of the final treatment plan. Patients will be offered a visit to the VR-room to familiarize themselves with what they can anticipate in the VR-condition. They can also contact the first author or the independent expert for more information. After the treatment plan is discussed with the patient, interventions that are indicated can take place prior to the start of the study (e.g., Re-ART module Stress Reduction, trauma-focused therapy). Pretreatment measurement takes place just before start of the study (Controlling Skills module). Upon finishing the questionnaires and forwarding them to the main researcher, patients will be informed about the condition they are assigned to.

#### Randomization

2.3.3

After obtaining written consent from the patient, the first author randomizes included patients using the online randomization program available at https://www.graphpad.com/quickcalcs/randomize2. Each time the program is utilized, it generates a distinct randomization list based on the date and time of usage. The randomization list will be accessible exclusively to the researchers.

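### The study team generates and holds the allocation sequence with a re-runnable web tool, and randomization is tied to consent rather than to a completed T1

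*Protocol article*

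**What the plan says.** All references are to the protocol article.

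- **Who assigns, and when (2.3.3 Randomization).** "After obtaining written consent from the patient, the first author randomizes included patients". The means is a public website.
- **How the list arises (2.3.3).** "Each time the program is utilized, it generates a distinct randomization list based on the date and time of usage".
- **Who sees it (2.3.3).** "The randomization list will be accessible exclusively to the researchers".
- **Who recruits (2.3.2 Recruitment).** "Therapists will approach patients who meet the study inclusion criteria". Consent is sought when the final treatment plan is discussed. Patients who want more information may turn to the first author or to an independent expert.
- **What may lie between consent and T1 (2.3.2).** Once the plan has been discussed, "interventions that are indicated can take place prior to the start of the study". The Stress Reduction module and trauma-focused therapy are the examples given. T1 is taken just before the Controlling Skills module.
- **When the patient learns the arm (2.3.2).** "Upon finishing the questionnaires and forwarding them to the main researcher, patients will be informed about the condition they are assigned to".
- **Who is analysed (2.7.1 Statistical analyses).** The ITT analyses cover every randomized patient, drop-outs included.
- **Planned size (2.3.1 Sample size).** 34 patients, 17 per condition, with no stated allowance for loss.

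**The concern.** Two features of the stated procedure are weaker than they need to be.

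**Control of the sequence.** The person who assigns can run the tool, can see its output and can be in touch with candidates. The article describes a tool whose result changes at every use, but not a step that makes one result final. The procedure as written therefore does not rule out replacing an unwelcome draw, and nothing in the text would show that this had happened. This is a route to selection bias, which no later covariate adjustment reliably removes.

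**Timing of assignment.** Disclosure to the patient is anchored to T1, but the assignment itself is anchored only to consent. If other treatment comes first, the interval may be long, and some patients may leave or cease to qualify: section 2.3.2 excludes those who receive concurrent interventions during the study. Each such patient is already in the ITT set. With no study measurement at either time point, the imputation in section 2.7.1.1 has no study outcome of that patient to build on.

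**Working it through.** **1. Control of the sequence.** The text allows two readings, and each leaves a gap.

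- *One list, made once and held.* The phrase about the list being accessible to researchers suggests this. The first author can then see coming allocations while answering candidates' questions. The list is also not said to be fixed before use, so it could be regenerated.
- *A fresh run for each patient.* No coming allocation exists to be foreseen, but a run can be repeated until it gives a different result.

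So either foreknowledge or re-drawing stays open to the assigner. Neither reading exposes the sequence to patients before T1, or to therapists who are not researchers.

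**2. Timing.** The order that the article permits is: consent at the treatment-plan discussion; randomization at some time after consent; possibly other interventions, of unstated length; T1; disclosure. Randomization may fall anywhere between consent and disclosure. Only if it falls after T1 does every ITT patient have at least a baseline.

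**3. Size of the timing problem.** The plan's own figure is reproduced first. Inputs from section 2.3.1: f = 0.25, alpha = 0.05, m = 2 measurements, k = 2 groups, correlation rho = 0.5, epsilon = 1.

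For the within-between interaction:

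- noncentrality: lambda = f² × N × m / (1 − rho)
- degrees of freedom: df1 = (k − 1)(m − 1) = 1 and df2 = (N − k)(m − 1) = N − 2
- power = probability that a noncentral F(df1, df2, lambda) exceeds the 95th percentile of the central F(df1, df2)

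At N = 34: lambda = 0.0625 × 34 × 2 / 0.5 = 8.5, df2 = 32, power = 0.807. At N = 32 power is 0.781, below 0.80. The smallest even N that reaches 0.80 is therefore 34, as stated.

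The article gives no rate of loss between randomization and T1, so a range of 5% to 30% is assumed. Remaining patients are 34 × (1 − loss), rounded down:

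| Assumed loss before T1 | Patients with T1 data | lambda | Power |
|---|---|---|---|
| none | 34 | 8.5 | 0.807 |
| 5% | 32 | 8.0 | 0.781 |
| 10% | 30 | 7.5 | 0.753 |
| 20% | 27 | 6.75 | 0.704 |
| 30% | 23 | 5.75 | 0.628 |

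These figures assume that 34 patients are randomized, that those lost are not replaced, and that everyone with a T1 also has a T2. Drop-out during treatment would come on top.

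**The case against.** The strongest reply is that concealment is planned where it usually matters most. Therapists, not the first author, approach patients; assignment follows written consent; the list is restricted to researchers; and patients hear their arm only after T1 has been completed and sent in. An independent expert is also available to them. All of this stands, and it limits the concern to the study team.

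Three stronger inferences are tempting, and the document does not support them.

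- *Allocation is neither concealed nor reproducible.* The first half ignores the safeguards just listed. The second does not follow either: a tool seeded by date and time gives a new list at each run, but a list saved once can be audited. The article does not say whether it is saved.
- *Patients are randomized at consent, long before T1.* Section 2.3.3 says after consent, and the prior interventions are optional. Early assignment is permitted, not prescribed.
- *The arms will be badly unbalanced.* This needs a fresh unrestricted draw for each patient, which the text does not state. Even then the cost is small: power is 0.795 at 14 against 20 and 0.771 at 12 against 22.

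A reader might also take the first author and the main researcher, who receives the T1 forms, to be one person. That is likely but not stated, and the point does not rest on it.

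Finally, an article may leave seed, block sizes and custody of the list to the full protocol. That is fair for those details. But this article does state who assigns, with what tool, who sees the list and which event precedes assignment. The comment concerns that stated procedure, for which a better one is readily available.

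**Conclusion.** The point holds in limited form. The sequence is generated and held within the study team by someone whom candidates may contact, with a tool that can be re-run. No single locked list and no holder independent of patient contact is stated. The text gives no sign that re-drawing or selective inclusion occurs, and any resulting bias cannot be sized from the document.

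Separately, assignment is not fixed relative to T1. The procedure therefore permits randomized patients who belong to the ITT set without any study outcome data. If 5% to 30% were lost in this way, power would fall from 0.807 to between 0.78 and 0.63. That range rests on an assumed rate and on the plan's own effect size and correlation. If assignment is in practice made after T1, this part of the problem disappears, and the text should say so.

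This should be changed because the remedy costs almost nothing. It is not evidence that the trial's allocation is invalid.

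**What to change.** Amend section 2.3.3 to state that:

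1. one list is generated once, preferably in randomly varying blocks, and is archived before further enrolment;
2. an existing colleague without patient or therapist contact holds it, or sequentially numbered sealed envelopes are used;
3. each patient is randomized only after eligibility has been reconfirmed and the T1 questionnaires have been logged.

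If a locked list already exists, one sentence saying so settles the first item.

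The cost is a short set-up by existing staff and a change of wording. Patients already learn their arm after T1, so nothing changes for them. The only downside is a short step between T1 and the first session. The third item also means that losses before T1 occur before randomization, so they no longer enter the ITT set.
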